#### Fetus/infant:

There is not data on use of this medication during pregnancy so the effects on a fetus/unborn child are not known. The study medication may cross the placenta and get to the fetus/unborn infant exposing the fetus to the study medication. It is unknown whether a fetus/unborn infant whose mother took LDV/SOF during pregnancy will develop normally or have side effects.

Obtaining blood samples from the infant may cause them to cry, cause bleeding, bruising or a clot and may be distressful to watch the infant have their blood drawn.

### **13.3.2 Benefits**

This study is a safety study of use of LDV/SOF in pregnancy and as such the study medication may not treat HCV in pregnancy as it may not be the correct dose. Participants and others may benefit in the future from information learned from this study. Specifically, information learned in this study may lead evidence based guidance for the treatment of chronic hepatitis C infection in pregnancy and prevention of perinatal HCV transmission.

### **13.4 Informed Consent Process**

Written informed consent will be obtained from each study participant prior to performing study procedures. In obtaining and documenting informed consent, the study investigators will comply with applicable local and US regulatory requirements and will adhere to GCP and to the ethical principles that have their origin in the Declaration of Helsinki. Participants may be provided with a copy of the informed consent form if they chose.

The informed consent process will cover all elements of informed consent required by research regulations. In addition, the process specifically will address the following topics of importance to this study:

- The unknown safety and proven efficacy of the study medications
- The importance of daily adherence to the study medication
- The importance of adherence to the study visit and procedures schedule
- The potential medical risks of study participation (and what to do if such risks are experienced)
- The potential social harms associated with study participation (and what to do if such harms are experienced)

- The benefits of study participation
- The distinction between research and clinical care
- The right to withdraw from the study at any time

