## 2.5 Rationale for Study Design

There is currently no experience with LDV/SOF in pregnant women, although based on the animal model data submitted to the FDA, this drug combination was given a pregnancy category B designation, meaning that there were no effects in on fetal development observed in rats and rabbits with doses higher than those given for treatment of hepatitis C in humans. Before larger scale treatment studies can be undertaken, it will be necessary to assess whether the pharmacokinetics of the drugs are similar in pregnant and nonpregnant women, and whether the trajectory of viral response to treatment is similar to that observed in nonpregnant women, given the higher viral loads observed during pregnancy. This pilot study is designed to address those knowledge gaps. We propose a single-arm, open label Phase 1 study of chronic hepatitis C treatment during pregnancy of 15 HCV (genotype 1, 4, 5 or 6)-infected pregnant women with a 12-week course of LDV/SOF. We propose a 12-week course because it is known HCV RNA concentrations are higher during pregnancy, thus a longer course will decrease the risk of HCV treatment failure. We will begin treatment during the second trimester, therefore eliminating the risk of LDV/SOF exposure to the fetus during organogenesis. Additionally, this will allow adequate time for treatment course completion by delivery.

The study will be completed in 10 or 11 visits (7 maternal visits, delivery visit and 3 infant visits) which should easily align with prenatal and postpartum visits (Table 1). We plan to screen patients between 14+0 and 22+6 weeks of gestation confirmed by ultrasound by the time of their Enrollment visit who are known to be HCV antibody positive. An HCV RNA level to confirm the patient is actively infected with HCV as well as an HCV genotype will be obtained. A full laboratory evaluation of liver function including CBC, PT/INR, hepatic panel, creatinine, creatinine kinase and lipase will be obtained, to evaluate for renal failure and decompensated cirrhosis. A Hepatitis B

Virus (HBV) panel will be performed to test all patients for evidence of current or prior HBV infection before initiation of HCV treatment. Medical history and demographic information will also be collected at screening. If the following inclusion and exclusion criteria are met, then the patient will be enrolled into the study between 23+0 and 24+6 weeks' gestation and initiated on a 12 week course of LDV/SOF.

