#### **3.2 Secondary Objectives**

1. To determine the rate of SVR12 of hepatitis C virus genotype 1, 4, 5 or 6 with LDV/SOF FDC treatment for 12 weeks during pregnancy.
2. To evaluate the maternal and neonatal safety of hepatitis C treatment with LDV/SOF FDC during pregnancy.

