### **10.5.2 Analysis of SVR12**

Outside of pregnancy, 96% of patients treated with LDV/SOF for 12 weeks obtained an SVR12. In this pilot study, we estimate that at least 14 out of the 15 chronically HCV-infected pregnant women will have a SVR12 after treatment. Participants who do not complete the treatment course or report low adherence will be excluded from the analysis.

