## 13.3 Risk Benefit Statement

### 13.3.1 Risks

#### General/Maternal

As with any research study, there may be adverse events or side effects for the maternal participant or the fetus/infant that are currently unknown and certain of these unknown risks could be permanent, severe or life-threatening.

There are no studies of LDV/SOF in pregnant women. There have been animal studies done in rats and rabbits as detailed in section 2.4.2. No effects on fetal development have been observed in rats and rabbits at the highest doses tested. However, animal reproductive studies are not always predictive of human response.

It is also not known if LDV/SOF is present in human breast milk. If the participant delivers while still on study medication and intends to breast feed, study medication will be discontinued and HCV resistance testing will be done at the next study visit.

There is a potential risk that the hepatitis virus may become resistant to LDV/SOF because the dose may not be adequate for treating pregnant women with hepatitis C or if the participant does not complete the entire 12 weeks of study medication. If resistance occurs, this may limit the choices of effective therapy after pregnancy for the participant and/or possibly her infant.

The following side effects have been associated with the use of oral LDV/SOF used daily for 12 weeks of duration in men and non-pregnant women:

|         | Percentage of Participants
N=539 |
|---------|-------------------------------------|
| Fatigue | 13%                                 |

|          |     |
|----------|-----|
| Headache | 14% |
| Nausea   | 7%  |
| Diarrhea | 3%  |
| Insomnia | 5%  |

There are risks of alterations in laboratory values with the use of this medication. Previous studies have shown the following:

Bilirubin Elevations: Bilirubin elevations of greater than 1.5x the upper limit of normal were observed in <1% of subjects treated with LDV/SOF for 12 weeks.

Lipase Elevations: Transient, asymptomatic lipase elevations of greater than 3x the upper limit of normal were observed in 2% of subjects treated with LDV/SOF 12 weeks.

Creatine Kinase: Creatine kinase was not assessed in Phase 3 trials of LDV/SOF FDC. Isolated, asymptomatic creatine kinase elevations (Grade 3 or 4) have been previously reported in subjects treated with sofosbuvir in combination with ribavirin or peginterferon/ribavirin in other clinical trials.

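### Section 13.4 lists efficacy as proven among the consent topics without limiting this to non-pregnant patients, which is inconsistent with 13.3.1, 13.3.2, 2.5 and 3.2

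*Protocol*

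**What the plan says.** Section 13.4 of the protocol first states that consent will cover the elements that regulations require. It then adds that "the process specifically will address the following topics of importance to this study". The first item on the list that follows is "The unknown safety and proven efficacy of the study medications". No population is attached to either half of the phrase. Later items on the same list include the medical risks of taking part and the benefits of taking part.

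Four other places in the protocol describe what is known about this drug in pregnancy:

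- Section 13.3.2 (Benefits): "the study medication may not treat HCV in pregnancy as it may not be the correct dose".
- Section 13.3.1 (Risks, General/Maternal): "There are no studies of LDV/SOF in pregnant women". The virus might become resistant "because the dose may not be adequate for treating pregnant women with hepatitis C".
- Section 2.5 (Rationale for Study Design): "There is currently no experience with LDV/SOF in pregnant women".
- Section 3.2 (Secondary Objectives), first item: "To determine the rate of SVR12 of hepatitis C virus genotype 1, 4, 5 or 6" with 12 weeks of treatment during pregnancy.

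On efficacy in other patients, 10.5.2 says: "Outside of pregnancy, 96% of patients treated with LDV/SOF for 12 weeks obtained an SVR12".

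**The concern.** The protocol treats efficacy in pregnancy as an open question. It gives two reasons: exposure may differ in pregnancy, so the dose may fall short, and viral load is higher in pregnancy. The SVR12 rate in pregnant women is accordingly an endpoint of the trial. A consent topic that calls efficacy proven, with no qualification, reads as though that question were settled.

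Efficacy carries weight in the decision a woman is asked to make. Section 13.3.1 tells her that resistance could narrow later treatment choices for her and possibly her infant, and that effects on the fetus are unknown. She sets those risks against the chance of cure. If the chance of cure is described too strongly, or described one way under one topic and another way under the next, that comparison is distorted. Consent precedes every screening procedure (7.2), so the wording bears on everyone approached for consent and not only on the 15 women the trial aims to enrol.

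**Working it through.** There is no figure to recompute. The check sets the passages side by side and asks whether any reading of 13.4 is consistent with all of them.

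**1. Force of the statement.** The list in 13.4 is introduced by *will address*. It directs what consent must cover and is not background text. It remains a list of topics, however, and supplies no script.

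**2. What the protocol supports, by population.**

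| | Outside pregnancy | In pregnancy |
|---|---|---|
| Efficacy | Documented: ION-1, ION-2 and ION-3 (2.4.1); 96% SVR12 (10.5.2) | Not established: no studies (13.3.1), no experience (2.5), may not treat HCV (13.3.2), SVR12 rate to be determined (3.2) |
| Safety | Documented: Phase 3 safety in 1080 patients (2.4.1); side effects tabulated for 539 (13.3.1) | Unknown (13.3.1) |

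**3. Test each reading of the phrase in 13.4 (safety unknown, efficacy proven).**

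- Both halves refer to pregnancy. Unknown safety is correct; proven efficacy contradicts the right-hand column.
- Both halves refer to use outside pregnancy. Proven efficacy is correct; unknown safety contradicts the left-hand column.
- Safety refers to pregnancy and efficacy to use outside pregnancy. Both halves agree with the table, but the reader must change population in mid-phrase and nothing in the text signals the change.
- *Proven* is a slip for *unproven*. Both halves then agree with the pregnancy column.

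The first two readings conflict with the protocol. The last two do not, but each needs words that are not there: a population qualifier in one case, a corrected word in the other. The line as printed is therefore either wrong or incompletely qualified.

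**4. Does the expectation in 10.5.2 rescue the word?** That section expects at least 14 of 15 women to reach SVR12, which is 14/15 = 93%. This is a forecast carried over from non-pregnant results and is not evidence in pregnancy. It does not make efficacy proven for these participants.

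**5. What else the consent process must contain.** The same list requires medical risks and benefits to be covered. The protocol's own text on those topics, 13.3.1 and 13.3.2, states the uncertainty plainly. A process that follows all of 13.4 would therefore include the correct account as well. The likely result of following the list literally is conflicting information; a purely false message is less likely.

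**The case against.** The strongest reply has four parts.

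First, the phrase can be read as true. The drug is approved, its efficacy outside pregnancy is well documented, and what is new here is safety for mother and fetus. On that reading the line contrasts what is known about the drug with what is not. This is a fair account of what may have been meant, and nothing in the grammar excludes it. It does not remove the need for a qualifier, because the line does not say which population it has in mind.

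Second, the authors' position is not in doubt: 2.5, 13.3.1 and 13.3.2 all state the uncertainty, so the word may be a simple slip. That may be so. A slip in a direction about consent still needs correcting.

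Third, 13.4 is a topic list that also calls for risks and benefits, and other safeguards exist. The IRB approves the consent form before the study starts (13.1), comprehension of consent is assessed (Table 3, Appendix I), and women are encouraged to discuss treatment with their primary care provider before deciding (7.2). This stands, and it limits the consequence considerably.

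Fourth, the consent form is not available here, so what women are told cannot be seen. This also stands. A reader might infer from 13.4 that women would consent on a false statement of benefit, or that staff are told to say cure in pregnancy is established. The documents support neither: no sentence instructs staff to say this, and the text that would settle it is not at hand.

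**Conclusion.** The inconsistency is real. Section 13.4 calls efficacy proven without limiting the word to non-pregnant patients, while 13.3.1, 13.3.2, 2.5 and 3.2 treat efficacy in pregnancy as unknown and under study. This is a contradiction in consent wording and not a design choice; sample size, power, endpoints and analyses are untouched.

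The consequence is conditional. If 13.4 were carried into the consent discussion as worded, women could receive an overstated account of benefit or one that conflicts with the risk and benefit text. Whether that happens depends on the consent form and on how the discussion is conducted, neither of which can be checked from the protocol. If the wording did carry through, it would reach every woman consented: the planned 15, the replacements (5.1.2 expects no more than two, so up to 15 + 2 = 17 enrolled), and those who fail screening.

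The correction is worth making because the line is an operative consent direction, the participants are weighing fetal exposure and possible resistance, and the change costs almost nothing.

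**What to change.** Reword the first topic in 13.4 along these lines: *the unknown safety and unproven efficacy of the study medication in pregnancy (efficacy has been shown only outside pregnancy)*. Then confirm that the consent form and the consent comprehension assessment give the same account of efficacy as 13.3.1 and 13.3.2.

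The cost is one line of protocol text, submitted to the IRB as an amendment under 13.1, and a read-through of the consent materials. No visit, measurement, sample size or analysis changes.

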### **13.5 Participant Confidentiality**

All study procedures will be conducted in private, and every effort will be made to protect participant privacy and confidentiality to the extent possible. All study-related information will be stored securely at the clinical research unit. All participant information will be stored in locked areas with access limited to the clinical study staff. All laboratory specimens, study data collection, and administrative forms will be identified by coded number (PTID) only to maintain participant confidentiality. All records that contain names or other personal identifiers, such as locator forms and informed consent forms, will be stored separately from study records identified by code number following completion of the study. All local databases will be secured with password protected access systems. Forms, lists, logbooks, appointment books, and any other listings that link participants' ID numbers (PTID) to identifying information will be stored in a separate, locked area with limited access. Participants' study information will not be released without their written permission, except as necessary for review, monitoring, and/or auditing by the following:

- Representatives of the US Federal Government, including the US FDA, the US OHRP and other local and US regulatory authorities
- Representatives of Gilead Sciences
- Study staff
- University of Pittsburgh IRB
- University of Pittsburgh Research Conduct and Compliance office

### **13.6 Special Populations**

#### **13.6.1 Pregnant Women**

Pregnant women will be offered enrollment in this study in accordance with guidelines set forth in the US 45 CFR 46.

#### **13.6.2 Children**

Infant procedures will begin at the time of delivery if delivered at Magee-Womens Hospital or at iV1 visit if infant delivered outside of Magee-Womens Hospital in accordance with guidelines set forth in the US 45 CFR 46 and DAIDS policy (<http://www.niaid.nih.gov/LabsAndResources/resources/DAIDSClinRsrch/Documents/enrollingchildrenrequirements.pdf>).

### **13.7 Compensation**

Pending IRB approval, participants will be compensated for time and effort in this study, and/or be reimbursed for travel to study visits and time away from work. Reimbursement amounts will be specified in the informed consent form. Compensation may include parking/bus passes and additional incentives for making study appointments within the window period. If needed and desired, compensation for overnight stay during the PK-1, PK-2 and PK-3 visits will be provided to participants traveling over 2 hours one-way to Magee-Womens Hospital for their study visits.

### **13.8 Communicable Disease Reporting**

Study staff will comply with local requirements to report communicable diseases including HIV-1 identified among study participants to health authorities. Participants will be made aware of reporting requirements during the informed consent process.

### **13.9 Access to HIV-related Care**

#### **13.9.1 HIV Counseling and Testing**

HIV testing will be performed at Screening. HIV test-related counseling will be provided to all potential study participants who consent to undergo HIV-1 screening to determine eligibility for participation. Counseling will be provided in accordance with standard HIV counseling policies and methods. Participants are expected to have HIV screening as part of routine prenatal care at 28 weeks' gestation, and if clinically indicated during the study.

#### **13.9.2 Care for Participants Identified as HIV-Positive**

##### Identified as HIV-Positive Prior to Enrollment

An individual who has been identified as infected with HIV-1 will not be eligible to participate and will be referred to the Pittsburgh AIDS Center for Treatment (PACT).

##### Identified as HIV-Positive While on Study Medication

The participant will continue with the study medication and study procedures, and will be immediately referred to PACT.

### **13.10 Study Discontinuation**

This study may be discontinued at any time by Gilead Sciences, the US FDA, the OHRP, other government or regulatory authorities, or the University of Pittsburgh IRB.

## **14 PUBLICATION POLICY**

The University of Pittsburgh study investigators will be responsible for publication of the results of this study. The manuscript draft will be sent to Gilead Sciences 30 days prior to submission for their review and approval.

## **15 APPENDICES**

## APPENDIX I: SCHEDULE OF STUDY VISITS AND EVALUATIONS (Mother)

|                                         | SCR
(V1) | ENR
(V2) | PK1, PK2, PK3
(V3, V4, V5) | End of
Treatment
(V6) | Delivery** | Post treatment
(V7) |
|-----------------------------------------|-------------|-------------|-------------------------------|-----------------------------|------------|------------------------|
| ADMINISTRATIVE AND REGULATORY    |             |             |                               |                             |            |                        |
| Informed consent(s)                     | X           |             |                               |                             |            |                        |
| Assess informed consent comprehension   | X           |             |                               |                             |            |                        |
| Assignment of PTID                      | X           |             |                               |                             |            |                        |
| Locator information                     | X           | X           | X                             | X                           | X          | X                      |
| Demographic information                 | X           |             |                               |                             |            |                        |
| Eligibility assessment                  | X           |             |                               |                             |            |                        |
| Eligibility confirmation                |             | X           |                               |                             |            |                        |
| Reimbursement                           | X           | X           | X                             | X                           | X          | X                      |
| Record/ update AEs                      |             |             | X                             | X                           | X          | X                      |
| Schedule next visit                     | X           | X           | X                             |                             | X          | -                      |
| BEHAVIORAL                       |             |             |                               |                             |            |                        |
| HIV pre- and post- test counseling      | X           |             |                               |                             |            |                        |
| Protocol adherence counseling           |             | X           | X                             | X                           | X          | X                      |
| Medication use/adherence counseling     |             | X           | X                             |                             | *          |                        |
| In depth interview                      |             | X           |                               | X                           |            |                        |
| CLINICAL                         |             |             |                               |                             |            |                        |
| Medical history                         | X           | X           | X                             | X                           | X          | X                      |
| Concomitant medications                 | X           | X           | X                             | X                           | X          | X                      |
| Document pre-existing conditions        | X           |             |                               |                             |            |                        |
| Physical examination (full or modified) | X           | X           | X                             | X                           | X          | X                      |
| Assessment of fetal heart tones         | X           | X           | X                             | X                           |            |                        |
| Provide available test results          | X           | X           | X                             | X                           | X          | X                      |
| Collect Pregnancy Outcomes              |             |             |                               |                             | X          | X                      |
| LABORATORY                       |             |             |                               |                             |            |                        |
| HCV RNA viral load                      | X           | X           | X (PK1&2)                     | X                           | X          | X                      |
| HCV Genotype                            | X           |             |                               |                             |            |                        |
| HCV Resistance testing                  |             |             | *(PK2 only)                   | *                           | *          | *                      |
| HBV Testing                             | X           |             |                               |                             |            |                        |
| CBC                                     | X           |             | X (PK1&2)                     |                             |            | X                      |
| Creatinine                              | X           |             | X (PK1&2)                     |                             |            | X                      |
| Hepatic Function Panel                  | X           |             | X (PK1&2)                     |                             |            | X                      |
| Lipase                                  | X           |             | X (PK1&2)                     |                             |            | X                      |
| Creatinine kinase                       | X           |             | X (PK1&2)                     |                             |            | X                      |
| HIV serology                            | X           | *           | *                             | *                           | *          | *                      |
| PT/INR                                  | X           |             | X (PK1&2)                     |                             |            | X                      |
| SOF PK                                  |             |             | X                             |                             | ^          |                        |
| LDV PK                                  |             |             | X                             |                             | ^          |                        |
| Protein Binding Assay                   |             |             | X                             |                             | ^          |                        |
| STUDY MEDICATION                 |             |             |                               |                             |            |                        |
| Provision of Study Medication           |             | X           | X                             |                             |            |                        |
| Collect Remaining Study Medication      |             |             |                               | X                           |            |                        |

\*If clinically indicated

\*\*May be performed during hospital admission for participants who deliver at Magee or applicable procedures conducted by phone for participants who deliver at outside locations. For all participants, a chart review of the delivery records will be done as part of the Delivery Visit

^ If still on study medication at the time of delivery

